### Intervention

#### Theoretical perspective

It is suggested that the effectiveness of interventions are maximised when an appropriate theoretical framework is utilised to guide intervention development [28]. The multi-level intervention, described below, has been designed using social ecological models of health behaviour change. Social ecological approaches acknowledge the multiple interrelated influences on health behaviours across social, cultural, and environmental domains [29,30]. The social ecological framework has been identified as a suitable conceptual model for the design of physical activity interventions [31] and has been applied when describing correlates of children's physical activity behaviours [6,32]. Furthermore, school-based interventions grounded in such social ecological theory have been found to be effective in increasing physical activity levels of children by altering instructional practices and the school environment [33]. Drawing on a social ecological framework, the intervention aims to influence children's physical activity behaviour through the manipulation of mediators across the social, physical and organisational environment of childcare services [12,34]. Specifically, the intervention will target staff instructional practices and interactions with children (social), service physical activity policy and programming (organisational) and the characteristics and equipment available within play space (physical environment).

#### Physical activity intervention

The intervention components are consistent with the recommendations of the draft Australian National Physical Activity guidelines for children [6] and the Australian National Healthy Eating and Physical Activity Guidelines for Early Childhood Services [21]. The intervention has been designed and will be overseen by an advisory group with representation from the Department of Community Services, the New South Wales Health Department, Authorised Supervisors from local services, health promotion practitioners, paediatric researchers and physical activity experts. The intervention will be delivered by staff of participating intervention group long day care services. Based on evidence from descriptive and available experimental research to increase child physical activity levels and reduce time spent being sedentary in childcare [11,21,35], the intervention will comprise of the following components:

*1. Delivering structured fundamental movement skill development activities *[9,18,35-40]:

Service staff will deliver daily structured fundamental movement skills (FMS) activities. Fundamental movement skills are the building blocks to more advanced movement skills and specific sport skills [41]. Structured activity is defined as those that are teacher initiated. Each session will include a warm up activity, age and developmentally appropriate teacher led games focusing on one or more FMS, and a cool down activity.

*2. Increasing the number of children's opportunities each day to participate in physical activity *[9]:

Service staff will increase the opportunities provided throughout the day for children to participate in physically active play. This will occur through service staff programming and opportunistically initiating movement based group activities such as dance and group games. This will also include modifying planned activities to incorporate active movement such as transitions between daily activities (such as moving inside to eat lunch or washing hands) and including movement within typically sedentary activities (such as table play e.g puzzles or play dough).

*3. Increasing staff role modelling of active play and delivery of instructional practices *[1,12,21,35]:

Staff will be supported to become active participants during all child initiated free play (role modelling) and provide verbal guidance (prompts to extend active play) and encouragement (positive statements about children's activity) to children to increase physical activity levels.

*4. Providing children with a physical activity promoting indoor and outdoor physical environment *[11,12,35,42-44]:

Services will increase the variety of activity promoting resources and toys available to children in indoor and outdoor areas. This will include varying arrangements of specific portable equipment to maximise child utilisation and interest. Services will also promote physically active play through displays, photos, books and posters within the service.

*5. Limiting children's small screen recreation and sedentary behaviours *[6,21]:

Whilst at the service, the amount of time children spend watching or using electronic media will be limited according to current aged based recommendations[6]. The time children spend in sedentary activities will be limited to periods of less than 30 minutes at a time (except when eating meals or sleeping).

#### Intervention implementation strategies

The research team will implement a number of strategies to engage services and facilitate their implementation of the physical activity intervention. The strategies to support intervention delivery are based on an organisational and practice change theoretical framework [45] and are supported empirically [46-50]. Specifically, the intervention implementation support strategies will include:

*1. Provision of staff training *[51,52]

All staff from intervention services will be invited to participate in a six-hour workshop to facilitate the implementation of the intervention. The workshop will introduce key physical activity intervention messages and concepts, include demonstrations of intervention activities and familiarisation with intervention resources. The training will support integration of physical activity across other learning areas linking to the service's existing curriculum, programs and activities [12,18,20]. The content of the workshop has been piloted with long day care services in the New England Region of New South Wales, Australia.

*2. Provision of resources and instructional materials *[36]

All services will receive a package of resources and instructional materials to sufficiently equip staff to implement the intervention. Specifically, the resources will include: an intervention manual providing a program rationale and background, current recommendations and best practice guidelines for physical activity in childcare services; policy template; instructional handbooks and DVD with age and developmentally appropriate physical activity games and play based activities to encourage the development of FMS; laminated activity cards to be used in the classroom with visual and written instructions for setting up and facilitating play based FMS activities; and lanyards to be worn by staff during outdoor play with pictures of each FMS including prompts to support teacher demonstration and cues for appropriate teaching. Services will also receive a planning resource in which to develop and record strategies for an individualised service action plan.

*3. Follow-up support *[50,53]

Authorised Supervisors will receive two 15 minute telephone support calls and a two hour service visit from intervention support staff to support the ongoing implementation of intervention components. The telephone support will be provided to Authorised Supervisors at approximately four and 15 weeks post provision of staff training. The service visit will occur approximately seven weeks post training. During the follow-up contacts, intervention support staff will assist Authorised Supervisor to set goals and develop an action plan regarding intervention delivery, review goals and service progress, reinforce service level changes and assist with problem solving. Authorised Supervisors will be asked to document goals, action plans and progress in a booklet provided. Additionally, during the service visits, intervention support staff will discuss any issues that service staff may be experiencing regarding the provision of intervention support.

*4. Performance monitoring, and feedback *[50,53]

Information collected during support contacts with the service will be used to monitor adoption of intervention components. Aggregated and non-identifiable summaries regarding implementation performance will be distributed to all services following the service visit and second phone contact via a project newsletter. The newsletter will reinforce the intervention components services are implementing well, highlight areas where some services may require improvement, and provide supportive information or case studies to facilitate intervention improvement. Performance feedback regarding individual service implementation will also be provided by program intervention staff during the follow-up service contacts.

*5. Use of relevant and credible opinion leaders *[46,51,52]

Support to services to deliver the intervention will be provided by two qualified early childhood teachers. The first represents a well known early childhood training organisation with extensive experience in the provision of training and support for services, particularly with regard to issues of child health. The second is a local practicing Authorised Supervisor, early childhood teacher and University Lecturer. Both intervention support staff members were selected on the advice of the Program Advisory Group as they are well known, influential and respected experts in the field of physical activity and early childhood, and would be perceived as both a credible and reliable source of information by Authorised Supervisors and service staff.

*6. Securing executive support and endorsement *[46]

The importance and benefits of implementing the physical activity intervention will be communicated to Authorised Supervisors and staff during telephone support calls, service visits and through the dissemination of regular project newsletters describing the implementation success of other services. Authorised Supervisors will be encouraged to demonstrate executive level support for the implementation and integration of the physical activity intervention into usual service practice through the endorsement and dissemination of a service level physical activity policy to staff and parents, and discussing service physical activity practices at staff meetings.

### Control group

Participating services randomised to the wait list control group will not receive any intervention support or materials during the study period. All control services will be offered staff training, resources and follow-up support after completion of all follow-up data collection.

### Data collection procedures

Research staff involved in data collection will be blind to group allocation and participating services will be asked not to disclose their group allocation to data collection staff during data collection. To assess the effectiveness of blinding, field data collection staff will be asked to guess the group to which they suspect the service was allocated following collection of trial outcome data.

#### Long day care service operational characteristics

To describe the operational characteristics of participating long day care services information will be collected from the Authorised Supervisor via telephone interview during the recruitment process.

#### Parent and child demographics and physical activity

Parents will be asked to complete items assessing basic demographic information about their child and their child's usual outside of care physical activity on the participant consent form at baseline. At follow-up, parents will again be asked to complete the items assessing child physical activity outside of care via a form which they will return to their childcare service. Self reported physical activity data will be used to assess any physical activity displacement as a result of the intervention.

#### Intervention implementation

Information on the implementation of the intervention by staff at each service will be collected via a staff survey, completion of the Environment and Policy Assessment Observation (EPAO) instrument and an audit of service documents.

The pen and paper staff survey will be distributed to all teaching staff at each participating service by the research team two weeks prior to baseline and follow-up collection of physical activity data. The survey contains items developed by the research team and takes approximately ten minutes to complete. Surveys will be coded to ensure answers remain confidential. Completed surveys will be posted back to the research coordinator or collected by field staff when they visit the service for data collection. The survey will measure the extent to which staff within each service implemented the intervention components as intended.

The physical activity component of the EPAO [54] will be used to assess intervention delivery during a one day field observation of staff practices, and environmental characteristics. The EPAO will be conducted in intervention and control services at baseline and follow-up on the day of field data collection assessing child physical activity. Two trained research staff will visit each service. The first staff member will act as the observer and record observations using the observation tool on one class of children aged three to five years at each service. Where a service has multiple classes, one class will be randomly selected to be the subject of observations. Observations will take place between 9 am to 3 pm, the core hours of service operation. The second staff member will assist with pedometer placement, playground measurement and general administration. The EPAO has been used in both descriptive and intervention studies [2,54] and has previously demonstrated high inter-observer agreement (87.3%) [54].

As part of the EPAO, one research staff member will a conduct brief ten minute interview with Authorised Supervisors where key physical activity documents including service policies and any physical activity curriculum will be viewed and audited. Data collection will be rescheduled in instances where weather conditions disrupt usual service routines and prevent children from using outdoor space (e.g during wet weather or temperature extremes).

#### Physical activity

Data will be collected from children attending each intervention and control service on a day of the week negotiated between the Authorised Supervisor and the research team. All children participating in the study will be asked to wear a pedometer (model Yamax SW200 and SW7000) on one week day over a six hour measurement period between 9 am and 3 pm. For each service data will be collected on the same day of the week at baseline and follow-up.

Pedometers are unobtrusive battery-operated instruments that are lightweight and about the size of a match-box. Pedometers measure vertical oscillations of body movement [55], and provide a total count of accumulated movements over the data collection time period [56]. Pedometers have been identified as a suitable tool for large-scale studies given their low cost and feasibility [56,57]. Additionally, pedometers have been demonstrated to be an accurate and reliable method of measuring physical activity levels in children [56,58] and preschool aged children [6,56,59]. Participant burden associated with wearing a pedometer is minimal [59], furthermore, it has been found that pre-school age children are comfortable with the contact required to collect data utilising pedometers [56].

The procedures for fitting participants with pedometers will follow protocols utilised in previous studies with young children [42,56,58]. Specifically, pedometers will be attached by trained research staff to the clothing of children above the right hip and in line with the right knee. If children wear dresses, loose pants or shorts, the pedometer will be attached to a small adjustable elastic belt worn by children at the waist. Pedometers will be set to zero at the beginning of the measurement period. Total step counts will be collected by research staff at the end of the measurement period. Pedometer data collection will also be rescheduled in instances where weather conditions disrupt usual service routines.

#### Intervention acceptability

Information on the acceptability of the intervention and intervention resources will be collected through the inclusion of items in the staff survey at follow-up for intervention services only.

### Measures

#### Long day care service operational characteristics

Operational information sought from the service will include the number of years in operation, the number of enrolled and attending children aged three, four and five years, and the number of primary contact teaching staff.

#### Parent and child demographics and physical activity

Parents will be asked to report child age, Aboriginal and/or Torres Strait Islander status, gender, postcode of residence and parental education level on the participant consent form. Parents will also be asked about the usual number of days their child spends at long day care each week and the usual amount of time their child spends being physically active and participating in small screen recreation during weekdays outside of care hours. Items assessing demographic and time spent in physical activity and small screen recreation outside of care were based on those used in other population based surveys of pre-school age Australian children [60].

#### Intervention implementation

Triangulation will be used to assess the extent to which services implemented the intervention as intended. First, data from the staff survey will assess how often staff report delivering structured fundamental movement skill activities for three to five year olds; the inclusion of warm ups, cool downs and skill specific feedback in FMS activities and the usual amount of time that structured FMS activities run for. The survey will also assess the frequency with which service staff report delivering verbal prompts and participating in children's active play; the number of occasions per day that the majority of three to five year old children are sedentary for over 30 minutes at a time (excluding meal and nap times); and how often and how long three to five year old children participate in small screen recreation activities.

Second, the EPAO field study will provide observational information on key physical activity intervention components occurring at the service on the day of data collection. This will include the number of occasions and total minutes of outdoor play, teacher led physical activities and structured fundamental movement skills activities during the six hour observation period. The number of times during the observation period that staff deliver prompts to increase activity and make positive statements to encourage activity, the number of times staff join in children's active play, and the total minutes children spend in sedentary activities or small screen recreation. The observation will include identifying the presence of portable and fixed play equipment in indoor and outdoor areas, a description of the space available for indoor and outdoor play (limited room for active play, obstructed by furniture or equipment), and a checklist of features of the outdoor play space such as playground surfaces and markings, vegetation and the presence of physical activity displays, books and posters.

Third, data collected as part of the EPAO Authorised Supervisor interview and service audit will be used to assess the presence of a physical activity policy, support within the policy for limiting small screen recreation time, integrating physical activity into the curricula and the provision of daily fundamental movement skills activities.

#### Physical activity

The primary trial outcome is child physical activity, operationally defined as step counts per minute [35,42,56] as measured by pedometers over the six hour operational period of services, from 9 am to 3 pm.

#### Intervention acceptability

At follow-up, the intervention service staff survey will include items assessing the use, acceptability and satisfaction with the intervention training and support provided to staff and services as part of the intervention. The items will require staff to respond to a series of statements on a four point Likert scale ranging from 'strongly agree' to 'strongly disagree'. Acceptability items were developed by the research team based on previous assessments of staff acceptability in delivering health promotion programs [61].

### Sample size and power calculations

Assuming a step count per minute of 17 among children attending control services and an intra-class correlation of 0.1 [62] a sample size of approximately 280 children (140 per group) attending 20 services at the 6 month follow-up will be sufficient to detect a difference between intervention and control groups of 4 steps per minute with 80% power at the 0.05 significance level. Assuming that long day care services care for 30 children aged three to five years per day on average, a study participation rate of 65% will be required to obtain the desired sample given a 20% attrition rate at the follow-up assessments.

### Analysis

All statistical analyses will be performed with SAS (version 9.2 or later) statistical software. All statistical tests will be two tailed with an alpha value of 0.5. Descriptive statistics will be performed to describe the demographic and service characteristics of intervention and control groups at baseline. Similarly measures of intervention implementation will be described using descriptive statistics.

The effectiveness of the intervention on child physical activity will be assessed utilising an intention to treat approach. An intention to treat analysis includes all participants in the analysis based on the groups to which they were allocated, without excluding data based on missing outcomes or non-adherence [22]. Specifically, linear mixed models will be used to examine between group differences on the primary trial outcome. Such analyses account for the correlation between pre and post measures and adjust for clustering. Any differences in the characteristics of participants at baseline will be adjusted for in the final linear model.

To ensure the results are robust, a sensitivity analysis will be performed whereby participants' observations at baseline will be used as a substitute for any subsequent missing data. A per-protocol analysis will also be conducted with participants from services which have sufficiently implemented the intervention.

Acceptability of the intervention among staff of services will be assessed by collapsing Likert scale categories and reporting the percentage of staff who responded 'strongly agree' or 'agree' to each acceptability item.

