## Methods/Design

### Study Design

The study will employ a cluster randomised controlled trial design (see Figure 1). A sample of eligible long day care services in the study region will be randomly selected and approached to participate in the trial. Ten services will be randomly allocated to a service-level physical activity intervention, delivered over a 15 week period, and ten services will be allocated to a wait list control group. The primary trial outcome measure, mean child step counts per minute, will be collected at baseline and approximately 6 months following baseline data collection. Services allocated to the wait list control group will receive the intervention after the collection of all follow-up data.

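### The primary model's wording suggests a pre-post repeated-measures contrast, whereas the sample size powers the arm difference at 6 months; naming a baseline-adjusted 6-month contrast would protect and probably raise power

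*Protocol article*

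**What the plan says.** The Study Design section states that the primary outcome, mean step counts per minute, "will be collected at baseline and approximately 6 months following baseline data collection".

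The Sample size and power calculations section works at the second time point only. It gives "a sample size of approximately 280 children (140 per group) attending 20 services at the 6 month follow-up" and calls this "sufficient to detect a difference between intervention and control groups of 4 steps per minute with 80% power at the 0.05 significance level". Its inputs are introduced as "Assuming a step count per minute of 17 among children attending control services and an intra-class correlation of 0.1". It states neither a standard deviation nor a correlation between a child's, or a service's, two measurements.

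The Analysis section names linear mixed models for the between-group comparison of the primary outcome and adds: "Such analyses account for the correlation between pre and post measures and adjust for clustering". The only baseline adjustment it describes depends on differences in participant characteristics being found at baseline. It does not name an arm-by-time term, does not say whether the arms have separate or shared baseline means, and does not say which contrast is tested.

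**The concern.** A model has a pre-post correlation to account for when both waves are responses. If baseline steps were a covariate, they would sit on the other side of the equation. The Analysis wording therefore most naturally describes a joint model of both waves. The default treatment effect in such a model, with each arm's baseline mean left free, is the arm-by-time term, that is, the difference in change. That is a different contrast from the one powered, and its precision depends on a correlation that the sample size calculation never uses.

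At stake is power. Each wave is a single six-hour pedometer day, and the waves are about six months apart, so a modest correlation is plausible, although the document gives no figure. If the correlation of service means is below 0.5, a difference in change is less precise than a comparison that ignores baseline altogether. Baseline data already collected would then cost power. Using the same data as an adjustment to the 6-month difference cannot do worse than the plan in large samples.

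**Working it through.** **Inputs from the document.** Difference 4 steps per minute; 80% power; alpha 0.05; ICC 0.1; 140 children per group; 20 services, so m = 280/20 = 14 children per service. The Analysis section prints a different alpha ("All statistical tests will be two tailed with an alpha value of 0.5"). That is a separate matter, and 0.05 is used here.

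**The plan's own figure.** The design effect is 1 + (14 - 1) × 0.1 = 2.3, so the effective size is 140/2.3 = 60.9 per arm. No SD is stated, so the 80% cannot be reproduced independently. Back-solving gives SD = 4 / [(1.960 + 0.842) × √(2/60.9)] = 7.88 on the normal approximation. The comparison below does not need this SD. It starts from the stated 80%, equivalent to a standardised effect of 1.960 + 0.842 = 2.802, and rescales it.

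**Variance relative to a follow-up-only comparison.** With equal variance at both waves and the same children measured twice:

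- difference in change: 2(1 - R)
- baseline-adjusted or common-baseline 6-month contrast: 1 - R²

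The gap is 2(1 - R) - (1 - R²) = (1 - R)², which is positive for every R below 1. The ratio is 2/(1 + R).

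**Power.** Φ(2.802/√factor - 1.960). For R = 0.3:

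- change: 2.802/√1.4 = 2.368, and Φ(0.408) = 0.658
- adjusted: 2.802/√0.91 = 2.937, and Φ(0.977) = 0.836

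| R (assumed) | 2(1-R) | Power, change | 1-R² | Power, adjusted | Variance ratio |
|---|---|---|---|---|---|
| 0.2 | 1.60 | 60.1% | 0.96 | 81.6% | 1.67 |
| 0.3 | 1.40 | 65.8% | 0.91 | 83.6% | 1.54 |
| 0.4 | 1.20 | 72.5% | 0.84 | 86.4% | 1.43 |
| 0.5 | 1.00 | 80.0% | 0.75 | 89.9% | 1.33 |
| 0.6 | 0.80 | 87.9% | 0.64 | 93.8% | 1.25 |
| 0.7 | 0.60 | 95.1% | 0.51 | 97.5% | 1.18 |

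**What R is.** With randomisation by service, R is the pre-post correlation of service means, not the correlation between one child's two pedometer days. Let C be the correlation over time of the service effects and I that of children within services. Then

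R = [m × ICC × C + (1 - ICC) × I] / [1 + (m - 1) × ICC] = (1.4C + 0.9I)/2.3,

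and the overall child-level correlation is 0.1C + 0.9I. Setting R = 0.5 gives 1.4C + 0.9I = 1.15:

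- C = 0.8: I = (1.15 - 1.12)/0.9 = 0.033; child-level break-even 0.08 + 0.03 = 0.11
- C = 0.5: I = 0.5; child-level break-even 0.50
- C = 0.2: I = (1.15 - 0.28)/0.9 = 0.967; child-level break-even 0.02 + 0.87 = 0.89

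Two illustrations with assumed values:

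- C = 0.8, I = 0.4: child-level correlation 0.44, R = 0.64, power 91% for change and 95.5% for the adjusted contrast.
- C = 0.5, I = 0.2: child-level correlation 0.23, R = 0.38, power 71% for change and 86% for the adjusted contrast.

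**The case against.** The strongest reply is that the article never specifies the model under criticism. The sentence about pre-post correlation fits a common-baseline longitudinal model just as well, since that model also takes both waves as correlated responses. The outcome is defined as steps per minute, not change. The exact parametrisation is commonly left to an analysis plan, which is not shown. This stands. A reader might infer that the protocol commits to a difference in change and so has lost its 80% power. The document does not support that: it states no arm-by-time term or free baseline means, and it does not exclude a 6-month contrast.

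A second reply is that 0.5 is not a threshold for the child-level correlation. This also stands. If service effects are stable over time, even a weak child-level correlation leaves the change contrast above 80%; if they are unstable, a strong one may not. A weak correlation between a child's two pedometer days would therefore not by itself show that power is lost.

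A third reply is that free baseline means can be useful. The trial is open, and the Random allocation section does not say whether parental consent and baseline measurement come before services learn their group. If they do not, differential child recruitment could break the shared baseline expectation, and forcing a common mean could bias the estimate. This limits the choice of remedy but does not remove the point.

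The SD is no objection to the power figures, because it cancels. They are conditional only on the stated 80% being right.

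**Conclusion.** The point holds as an efficiency improvement, not as a demonstrated error. The Analysis wording leans towards a joint pre-post model with baseline adjustment only where imbalance is seen, while the sample size rests on "a difference between intervention and control groups of 4 steps per minute" at 6 months. If the tested effect is the unconstrained difference in change, power at R from 0.2 to 0.5 runs from about 60% to 80%, against 82% to 90% for the adjusted 6-month contrast. At larger R the change contrast keeps at least 80% and the gap narrows, but its variance is still 2/(1 + R) times that of the alternative.

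This rests on a model the article does not spell out, an R it does not give, equal variances at the two waves, the same children at both waves, and large-sample formulas. With 20 services the real gain would be slightly smaller. The ordering of the two contrasts does not depend on R in these formulas; the size of the gap does.

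**What to change.** State that the primary estimate is the arm difference at 6 months from the linear mixed model, with one baseline mean common to both arms and clustering by service. The covariance structure should allow correlation over time at both service and child level, so that the gain at the level of service means is realised. Children with only one of the two measurements stay in this model, in keeping with the intention-to-treat statement.

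The alternative is to model the 6-month value with the child's baseline steps per minute and the service-mean baseline as covariates, planned in advance and not contingent on imbalance. The two are not equivalent: the covariate version drops children without a baseline value, and the child's baseline alone need not deliver the full gain under clustering.

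The common-baseline version assumes that child consent and baseline measurement are not influenced by knowledge of allocation. The plan should say whether they precede disclosure to services. If they could be influenced, use the covariate version.

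The cost is a sentence or two of analysis wording and a small change in model code, with no new data.
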